**Tertiary Outcome Measure**

Individual non-cardiac cardiovascular outcome measures: ischaemic stroke; peripheral vascular disease; vascular dementia.

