**Study Design**

This will be a retrospective study of the RCGP-RSC cohort. The data available were collected between April 2005 and March 2015 ([name] to confirm). These will be analysed using Read v2 (5-bit) codes to identify patients by the inclusion and exclusion criteria. Laboratory sample data will be taken from the laboratory sample results collected by GP practices.

Inclusion: One or more serum phosphate measurements recorded before a cardiovascular event (primary myocardial infarction; acute coronary syndrome; revascularisation procedure; ischaemic stroke; peripheral vascular disease; vascular dementia), or recorded in patients without any cardiovascular event in the study period. Patients will be aged 18 years and older.

Exclusion: Patients who have already had primary myocardial infarction; acute coronary syndrome or a revascularisation procedure before any serum phosphate measurements have been recorded. Patients with pre-existing ischaemic stroke, peripheral vascular disease or vascular dementia will also be excluded.

Serum phosphate will be a linear variable or analysed further as a categorical variable by range. ‘Time zero’ will refer to the first available serum phosphate measurement of a patient. The time to any outcome measure will be recorded and associations between serum phosphate and outcomes will be analysed by cox-regression.

In patients where more than one serum phosphate measure is available, the mean average of up to the first five measurements from time zero and before any cardiovascular event will be recorded and used in this study.

Importantly, confounding factors for cardiovascular outcomes in all included patients will form part of this study. For each variable, the selected single measurement will be chosen before the outcome measure and as close to time zero as possible, subject to data availability. The exceptions are baseline eGFR and albumin:creatinine ratio – the mean of two measurements in each case will be taken.

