**Limitations**

The study population will only include patients that have had sufficient routine blood tests taken. This may introduce bias for increased risk of confounding co-morbidities amongst this group. Serum phosphate levels are influenced acutely and chronically by many factors including disease, exercise and diet - which independently influence cardiovascular risk. We aim to control for cardiovascular risk factors based on the QRISK2 model [6].

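### Outcomes count from the first phosphate with no minimum interval, so a test drawn while an event is already emerging can be scored as predicting it; a lagged analysis should be pre-specified alongside

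*Protocol*

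**What the plan says.** The timing rules are all in the Study Design section of the protocol:

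- **Origin and follow-up.** Time zero "will refer to the first available serum phosphate measurement of a patient. The time to any outcome measure will be recorded", and the associations are analysed by Cox regression.
- **Eligibility.** The timing condition on exposure is "One or more serum phosphate measurements recorded before a cardiovascular event", or a measurement in a patient with no event in the study period. No gap is required.
- **Exposure.** With repeat tests, "the mean average of up to the first five measurements from time zero and before any cardiovascular event will be recorded and used". Values may run up to the event.
- **Prior disease.** Earlier cardiac events are excluded, and "Patients with pre-existing ischaemic stroke, peripheral vascular disease or vascular dementia will also be excluded". Patients are identified by Read codes.

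The same origin serves the cardiac outcomes and the tertiary ones: "ischaemic stroke; peripheral vascular disease; vascular dementia". The Limitations section states: "Serum phosphate levels are influenced acutely and chronically by many factors including disease, exercise and diet". It adds that inclusion depends on having had enough routine blood tests, and gives control for QRISK2-based risk factors as the aim.

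**The concern.** The Research Question asks whether phosphate independently predicts new events, and the Hypothesis concerns event onset. Both presuppose that phosphate was measured before the disease process that ends in the coded event could have affected it. The protocol secures only that the test precedes the code.

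Blood tests in routine care are often prompted by illness. If emerging disease both prompts the test and shifts its value, early events will be associated with phosphate even where phosphate carries no information about later risk. The exclusions remove coded disease; undiagnosed disease passes through. Peripheral vascular disease and vascular dementia usually develop well before a diagnosis is entered, so they are the most exposed.

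The Limitations section treats selective testing as a source of confounding co-morbidity and answers it with covariates. Adjusting for risk factors does not undo an effect of the emerging outcome on the exposure. At stake is what a significant phosphate hazard ratio can be taken to show.

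**Working it through.** **What the protocol gives.** A source population of about 1,250,000, up to ten years of observation, and significance at P < 0.05. It gives no number with a phosphate result, no event count and no effect size, so there is no figure to reproduce. Everything below is illustrative.

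**1. Excess early events.** Assumed: mean follow-up 5 years; early window 90 days (0.25 year); early event rate raised by a factor m because some tests are drawn in work-up; hazard ratio 1.5 per SD among the work-up events and 1.0 among all others; 150,000 patients × 5% risk = 7,500 events.

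Only the excess early events are work-up driven; the background early events would have occurred anyway.

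- Share of events = (m − 1) × 0.25 / (m × 0.25 + 4.75)
- Spurious log HR ≈ share × ln 1.5 = share × 0.405
- SE ≈ 1/√7,500 = 0.0115 (one standardised covariate; covariate adjustment would enlarge it)

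Results:

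- m = 3: 0.50/5.50 = 9.1%; log HR 0.0369; HR 1.04; z = 3.2
- m = 2: 0.25/5.25 = 4.8%; log HR 0.0193; HR 1.02; z = 1.7, not significant
- Break-even: z = 1.96 needs a share of 1.96 × 0.0115/0.405 = 5.6%, which is m of about 2.2

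**2. Range of inputs.** If a fraction f of events has phosphate shifted by d SD and the true HR is 1, log HR ≈ f × d. The events needed for an 80% chance of P < 0.05 are (1.96 + 0.84)²/(f × d)².

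- f = 5%, d = 0.5: HR 1.025; about 12,560 events
- f = 10%, d = 0.5: HR 1.05; about 3,140 events
- f = 20%, d = 0.5: HR 1.105; about 785 events
- f = 20%, d = −0.5: HR 0.905; about 785 events

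**3. What a lag does.** One simulated data set per row, true HR 1. Assumed: 60,000 patients, background hazard 1% per year, censoring uniform from 0.5 to 10 years, mean time to event 0.25 year in patients tested during a work-up.

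| Tested in work-up | Shift (SD) | Work-up share of events | HR, no lag | HR, 6 months (p) | HR, 12 months (p) | Events kept at 12 months |
|---|---|---|---|---|---|---|
| 0.5% | +0.5 | 8.6% | 1.05 | 1.03 (0.12) | 1.01 (0.48) | 2,393/3,295 = 73% |
| 1% | +0.5 | 17.0% | 1.10 | 1.04 (0.043) | 1.02 (0.29) | 2,497/3,687 = 68% |
| 1% | −0.5 | 16.9% | 0.92 | 0.98 (0.28) | 0.99 (0.56) | 2,348/3,534 = 66% |
| 1% | +0.3 | 16.5% | 1.08 | 1.05 (0.014) | 1.04 (0.058) | 2,440/3,616 = 67% |

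Each run carries sampling error of about 0.017 to 0.020 on the log scale. The last row shows it: the formula in step 2 predicts HR 1.05 (0.165 × 0.3 = 0.050), and the run gave 1.08. The short work-up time is assumed, so the table does not inform the lag for slow-onset outcomes.

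**The case against.** The strongest reply is that starting follow-up at the first measurement is a conventional cohort origin, that lagged analyses are often left to the SAP, and that this protocol says expert statistical advice will be sought. It is right that the origin is neither misstated nor contradicted. But the protocol itself fixes the origin, the eligibility timing and the exposure window, and itself concedes the acute disease effect, so the remedy belongs beside those rules.

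Other points stand in part:

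- Laboratory data come from GP practices, which narrows the work-up route for acute, hospital-managed events. Vascular dementia and peripheral vascular disease are tertiary outcomes, so the primary composite is less exposed.
- Albumin and BMI are among the covariates and may capture some illness and nutrition. Averaging can dilute one abnormal value, but values drawn shortly before the event can also enter the mean.
- A phosphate value shifted in a prodrome may still forecast the later diagnosis. For those events the problem is what the prediction means, not that none exists.

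A reader might infer more than the protocol supports:

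- **That same-day events count.** The measurement must come before the event, so on a strict reading they do not; an event the next day does.
- **That hospital events are entered late under the wrong date.** This is possible, but the protocol does not say so and the point does not need it.
- **That any modest early excess yields a significant result.** Applying the 1.5 ratio to every early event gives shares of 0.75/5.5 = 13.6% (z = 4.8) at a tripled rate and 0.5/5.25 = 9.5% (z = 3.3) at a doubled rate. That counts background events as work-up driven.

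**Conclusion.** The point holds as a gap in interpretation that is cheap to close. The protocol counts any outcome recorded after the first phosphate, with no minimum interval, and its stated remedy does not address reverse causation.

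Neither the size nor the direction of the bias follows from the protocol. On the assumptions shown, the spurious hazard ratio is about 1.04 per SD (z about 3.2) at a tripled early rate. At a doubled rate it is about 1.02 and not significant. Over the wider range of 5% to 20% of events affected and shifts of −0.5 to +0.5 SD, it lies between about 0.90 and 1.11.

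This does not show that the analysis from time zero is invalid, or that the lagged analysis must replace it as primary. It shows that the unlagged estimate alone cannot separate prediction of new events from detection of events already under way.

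**What to change.** In Study Design, keep the analysis from time zero and add a pre-specified landmark analysis reported beside it for every outcome:

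- Fix one lag per outcome in advance: for example 6 or 12 months for the cardiac outcomes and ischaemic stroke, and a single longer lag such as 24 months for peripheral vascular disease and vascular dementia.
- Drop events and person-time before the landmark.
- Let only phosphate values taken before the landmark enter the mean. This guarantees the full gap for the first value only; a variant using the first value alone would guarantee it for the whole exposure.
- State that a phosphate association will be described as predicting new events only if it persists in the lagged analysis. Judge persistence on the estimate and its interval, since loss of significance alone may reflect fewer events.

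The cost is a few sentences and one refit per outcome on the same data. The downside is precision: about one third of events were lost at 12 months in most of the simulated scenarios. In the second row of the table that widens the standard error by √(3,687/2,497) = 1.22. A longer lag would cost more. The lag lengths are judgements; in that same row a 6-month lag still left HR 1.04.

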**Data source and Sample Size**

RCGP-RSC data will be used for this study. These are from a database of coded primary care data from 135 UK General Practitioner (GP) practices – total population of approximately 1,250,000 patients. A large sample size is necessary for this study due to the variability in serum phosphate concentrations and the duration of the observational period (up to ten years).

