**Confounding variables considered**

Demographics: Age (time zero); gender; ethnicity; body weight and height (to calculate body mass index); BMI; postcode-derived deprivation score (PDDS) (UK Index of Multiple Deprivation 2007); smoking status.

Co-morbidities: Cardiovascular disease (primary myocardial infarction; acute coronary syndrome; revascularisation procedure; ischaemic stroke; peripheral vascular disease; vascular dementia); HbA1c; hypertension (SBP).

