**Statistical analysis**

Numerical data will be refined by excluding values beyond physiological limits. Data will be analysed using the statistical package R, with P values <0.05 being regarded as statistically significant. Expert statistical advice will be sought with the aim of using cox regression models to determine the association between serum phosphate and cardiovascular events, adjusting for the known cardiovascular risk factors. Cox proportional hazards multivariate models will also be constructed to provide a time-event analysis. A backwards stepwise elimination of variables approach will help to refine the model and evaluate the contribution of each variable towards the outcome measures.

Ethical considerations

Approval has been sought from the RCGP for the RSC database to be used for such research projects. Our study is retrospective and observational over anonymised patient data. The study involves no clinical interventions, no patient contact and no breach of confidentiality. The results of the study will be submitted for publication to a peer-reviewed journal.

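### Time zero can fall anywhere in a ten-year window, but calendar year of entry is not among the named adjustment variables, which leaves a small, avoidable risk of confounding the phosphate hazard ratio

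*Protocol*

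**What the plan says.** Study Design gives the data window: "The data available were collected between April 2005 and March 2015" (the dates are still marked for confirmation). Time zero "will refer to the first available serum phosphate measurement of a patient", so it differs between patients and can fall anywhere in that window. The analysis runs from that point: "The time to any outcome measure will be recorded and associations between serum phosphate and outcomes will be analysed by cox-regression".

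Adjustment is described in several places:

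- Confounding variables considered opens with "Demographics: Age (time zero); gender; ethnicity; body weight and height" and goes on to BMI, deprivation, smoking, HbA1c, blood pressure and prior cardiovascular disease.
- Biochemical variables required lists the laboratory covariates.
- Statistical analysis speaks of "adjusting for the known cardiovascular risk factors" and plans backward elimination.
- Limitations adds: "We aim to control for cardiovascular risk factors based on the QRISK2 model".
- Intended output sets out a blank table of 20 variables, to be filled for each outcome.

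None of these names calendar year or period of time zero, as a covariate, a stratum or a time scale. Age at time zero is there, but two patients of the same age can enter almost ten years apart.

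**The concern.** With the clock started at each patient's first phosphate, one Cox risk set compares patients who are equally far into follow-up but may have entered in very different calendar years. If the event rate or its coding shifted over the decade, entry year predicts the hazard. If measured phosphate also shifted, because assays changed or because different kinds of patient came to be tested, entry year is also associated with the exposure. It is then an ordinary confounder.

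Both links are plausible here. Phosphate comes from routine results collected by 135 practices, and no standardisation across laboratories or over time is described. The Limitations section itself accepts that inclusion depends on who has blood tests taken.

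At stake is a modest shift in the main estimate. In a cohort this large, an association of a few per cent per SD may be declared significant, so a shift of that order can matter. The plan names its covariates and then eliminates from them, and a variable never offered to the model cannot be retained.

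**Working it through.** **Plan's own figure.** There is none. The protocol gives no effect size, event count, phosphate SD or calendar trend.

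**Inputs**

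- From the protocol: a ten-year window, and entry at the first phosphate.
- Assumed: entry spread evenly; phosphate SD 0.19 mmol/L within year; event rate falling by a fraction *d* = 3-5% a year; mean measured phosphate rising by *g* = 0.005-0.02 mmol/L a year.

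**Step 1: simple omitted-covariate approximation**

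Shift in log HR per SD = ln(1 − d) × SD_year × r, where SD_year = 10/√12 = 2.89 and r = 2.89g / √(0.19² + (2.89g)²).

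Example (5%, 0.02): 2.89 × 0.02 = 0.0577; r = 0.0577/0.1986 = 0.291; shift = −0.0513 × 2.89 × 0.291 = −0.043, a multiplier of 0.958. With g = 0, r = 0 and the shift is nil whatever the event trend. With d = 0 it is also nil.

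**Step 2: why Step 1 overstates the shift**

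Step 1 uses the spread of entry years over the whole cohort, a variance of 100/12 = 8.33. At follow-up time *t* only those who entered in the first 10 − t years can still be at risk, so the variance within the risk set is (10 − t)²/12. Numbers at risk, and so events, are roughly proportional to 10 − t. The event-weighted average variance is therefore

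∫(10 − t)³/12 dt ÷ ∫(10 − t) dt, over 0 to 10, = 208.3/50 = 4.17,

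which is half of 8.33. The shift should be about half the Step 1 figure.

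**Step 3: simulation**

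No true phosphate effect, even entry, SD 0.19, censoring at year 10, n = 20,000, 30 replicates. Each replicate was fitted with and without entry year and the two log HRs were compared within replicate.

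| Event decline, phosphate drift | Step 1 log HR shift (multiplier) | Simulated log HR shift |
| --- | --- | --- |
| 3%, 0.005 | −0.007 (0.993) | −0.0035 |
| 3%, 0.01 | −0.013 (0.987) | −0.008 |
| 5%, 0.01 | −0.022 (0.978) | −0.012 |
| 5%, 0.02 | −0.043 (0.958) | −0.024 |

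The Monte Carlo standard error of each simulated shift is at most 0.0013. A repeat with the same inputs gave about −0.003 to −0.025, that is, multipliers of 0.997 to 0.975.

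A smaller simulation (8 replicates, SD 0.18) compared averaged hazard ratios and had Monte Carlo error of about 0.01 on the HR. Its contrast at 0.01 drift was within noise. The larger paired comparison resolves that contrast.

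**Step 4: size against a modest association**

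ln(1.05) = 0.0488 and ln(1.10) = 0.0953. At the extreme, −ln(0.975) = 0.0253, which is 52% and 27% of these. In the middle case (5%, 0.01), 0.012 is 25% and 13%.

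**Direction.** A falling event rate with rising phosphate pulls the HR down and masks a positive association. If both fall, or both rise, the HR is pushed up.

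**The case against.** **This belongs in an analysis plan.** Stratifying by entry year is a modelling detail. The Statistical analysis section is an outline, says expert advice will be sought, and rules nothing out. This has force: the protocol does not forbid calendar adjustment. But it does name its covariates, and this one is absent from a design that makes entry year vary by up to a decade.

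**The lists are not closed.** A reader might infer that the lists are a complete model specification, so that calendar adjustment is excluded. The document does not support that. Calcium is in the output table but not under Biochemical variables required, and prior cardiovascular disease is among the confounders but has no table row. A stratification variable yields no hazard ratio, so it would not appear in that table anyway. What stands is only that calendar year is named nowhere.

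**The bias is hypothetical.** It needs two trends that the protocol does not report, and both must survive adjustment. Covariates already planned, such as age, eGFR, albumin and lipids, would absorb part of any change in who is tested. This is correct, and the simulation does not include such absorption. The top drift is also severe: 0.02 a year is 0.20 mmol/L over ten years, more than the assumed SD of 0.19.

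**Two further inferences do not hold.** Putting the Step 1 extreme (0.958) against true HRs of 1.10 and 1.05 suggests that 45% to 88% of the effect is hidden, but that formula ignores how risk sets thin out. Nor is the link between entry year and maximum follow-up a separate bias: it affects the phosphate HR only under the same joint trends.

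**Conclusion.** The point holds as a minor, assumption-dependent weakness. Entry is open across ten years, and calendar year of time zero does not appear in the named adjustment variables or the model description. Confounding of the phosphate hazard ratio is possible in either direction, and is nil if either the event-rate trend or the phosphate trend is absent.

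Under the assumed ranges (3-5% annual decline, 0.005-0.02 mmol/L annual rise, SD 0.19, even entry, no other covariates) the HR per SD is multiplied by about 0.997 to 0.975. Only the extreme end reaches about 25-50% of the log HR for a true HR of 1.10-1.05.

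A reader might conclude that the planned estimate is biased. The protocol does not show this, because it gives no evidence of either trend. The case for acting is that the safeguard is nearly free.

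**What to change.** In Statistical analysis, state that every Cox model will either stratify the baseline hazard by calendar year of time zero or include year as a categorical covariate that is exempt from backward elimination. Name calendar year of time zero under Confounding variables considered.

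The cost is one line of model code and two short additions to the text. No new data are needed, since the date of first phosphate already defines time zero, and no patients are lost.

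The change reduces the bias but need not remove all of it. Assay changes may fall at different dates in different laboratories, and the exposure averages up to five measurements that may span several years, so the year of time zero tracks the assay period only in part.

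### Follow-up starts at the first phosphate, but the exposure is a mean of up to five values (at most four of them later) cut off by the patient's own event, so the analysis by range, and the linear one if phosphate drifts, is biased

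*Protocol*

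**What the plan says.** All the relevant rules stand in the protocol's Study Design section.

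- **Clock.** Time zero "will refer to the first available serum phosphate measurement of a patient".
- **Exposure.** For anyone with repeat tests, the rule is that "the mean average of up to the first five measurements from time zero and before any cardiovascular event will be recorded". No averaging window is given.
- **Entry.** A single value is enough: "One or more serum phosphate measurements recorded before a cardiovascular event".
- **Model.** "The time to any outcome measure will be recorded and associations between serum phosphate and outcomes will be analysed by cox-regression".
- **Form of the exposure.** "Serum phosphate will be a linear variable or analysed further as a categorical variable by range".
- **Covariates.** For each, "the selected single measurement will be chosen before the outcome measure and as close to time zero as possible". Baseline eGFR and the albumin:creatinine ratio are means of two measurements.

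Observation can last up to ten years (Data source and Sample Size), so the second to fifth values may fall years into follow-up. The protocol has no landmark, delayed entry or time-updated covariate, and its Limitations section does not raise the issue.

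**The concern.** A Cox model compares, at each event time, the covariate of the patient who has the event with the covariates of those still at risk. The covariate should be known by then. Here two things break that rule.

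1. **Future values.** A patient at risk in year 1 may be classified by values taken in year 4.
2. **Precision tied to the outcome.** Averaging stops at the event. A patient with an early event is represented by one noisy value, and a patient who stays event-free by a smoother mean of up to five. Noisy values fall into extreme ranges more often, so patients with events collect there even if phosphate has no effect.

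If phosphate also changes over time, the mean carries more of that change in patients followed for longer without an event, and this shifts the linear HR.

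The Background section treats both high and low phosphate as relevant to risk. A spurious excess at either end could therefore be read as a finding. A larger cohort would only make the artefact more precise.

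**Working it through.** The protocol gives no variance, testing interval, event rate, drift or category limits, so there is no figure to reproduce. Every numerical input below is an assumption.

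**Step 1. Precision.** The mean of k values has variance σ_b² + σ_w²/k, where σ_b is the between-person SD and σ_w the within-person SD. Its reliability is σ_b² / (σ_b² + σ_w²/k). With σ_b = σ_w = 0.13 mmol/L, reliability is k/(k+1): 1/2 = 0.50 for one value and 5/6 = 0.83 for five.

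**Step 2. Effect on ranges.** Take a mean of 1.1 and a low range below 0.85 mmol/L, that is 0.25 below the mean.

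- One value: SD = 0.13 × √2 = 0.184; z = 0.25/0.184 = 1.36; share in the range 8.7%.
- Five values: SD = 0.13 × √1.2 = 0.142; z = 0.25/0.142 = 1.76; share 4.0%.

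With the same underlying distribution, a patient with one value is about 2.2 times as likely to be classed as low. By symmetry the same holds for the high range above 1.35.

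**Step 3. Effect of drift.** With yearly tests, five values have a mean time of (0+1+2+3+4)/5 = 2 years. A drift of +0.01 mmol/L per year then adds 0.02 to a five-value mean and nothing to a single value. Event-free patients look higher, so the HR falls below 1.

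**Step 4. Simulation A, no true effect.** 4 replicates of 120,000 patients; events 1.2% per year; follow-up 0 to 10 years; σ_b 0.15, σ_w 0.12. Lowest and highest 5% against the middle 60%, under the protocol's mean:

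| Test interval | HR, lowest 5% | HR, highest 5% |
|---|---|---|
| 0.5 year | 1.13 | 1.15 |
| 1 year | 1.19 | 1.22 |
| 2 years | 1.25 | 1.26 |

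The first value alone gave 0.97 to 1.00, a 12-month landmark mean 0.97 to 1.00, and a time-updated cumulative mean 0.96 to 1.02. The linear HR per 0.15 mmol/L under the protocol's mean was 0.96, 0.93 and 1.05 for drifts of +0.01, +0.02 and −0.01 mmol/L per year.

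**Step 5. Simulation B, separate code, no true effect.** 40 replicates of 8,000 patients; σ_b = σ_w = 0.13; 0.7 repeat tests per year; hazard 0.01 or 0.03 per year; censoring uniform over 0.5 to 10 years; ranges below 0.85 and above 1.35. Patients with an event contributed about 2.9 values, those without about 3.6 to 3.7.

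| Drift per year | Linear HR per 0.13 mmol/L | HR, low range | HR, high range |
|---|---|---|---|
| 0 | 1.004 to 1.006 | 1.27 to 1.29 | 1.30 to 1.31 |
| +0.02 | 0.89 to 0.90 | 1.81 to 1.87 | 0.94 to 0.99 |
| −0.02 | 1.13 | 0.92 to 0.93 | 1.74 to 1.78 |

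With drift, the linear test rejected the true null in 72% to 100% of replicates. In the same runs the first value alone gave linear HRs of 1.001 to 1.005, and a 2-year landmark mean gave 0.998 to 1.009. Range HRs for these two lay between 0.95 and 1.02.

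**Step 6. Sensitivity of the size.** Further null runs without drift under the protocol's mean gave:

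- outer quartiles against the middle half: about 1.04 to 1.16, or 1.00 to 1.09 if half the patients have one value;
- extreme 5%: about 1.17 to 1.21, or 1.08 to 1.10 if half have one value;
- extreme 5% with σ_b 0.13 and σ_w cut to 0.06: 1.13 and 1.09, near simulation error;
- extreme 5% with everyone retested every 2 years: about 1.4 in one set of runs.

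**The case against.** **The linear analysis comes first and is sound.** The protocol names the linear form before the categories, and the single phosphate row in the Intended output table fits a linear term. For that form, with no true effect and no drift, the HR stays at about 1.00. This stands. A reader might infer that the exposure is spoiled in every outcome analysis, but the documents do not support that: the bias needs either categories by range, which are planned, or drift, which the documents neither give nor rule out.

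**It is not classic immortal time.** A reader might call it that. But no phosphate level requires survival, since everyone enters with one value, and without drift the error does not run in one direction. What survival decides is how many values are averaged. The accurate description is use of future values with outcome-dependent precision.

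**The size is assumed.** Category limits, SDs, testing rates, event rates and drift are all the reviewer's inputs. The artefact shrinks with wider categories or many single-value patients, and grows with sparse retesting of everyone. This stands, so the figures show a range and do not predict the bias in this database.

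**Detail may follow elsewhere.** The Statistical analysis section defers modelling to expert advice, and an analysis plan may exist. That softens the point but does not remove it, because the protocol itself fixes both the clock and the exposure, and these two conflict.

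**Averaging is a legitimate aim.** It reduces measurement noise. The fault lies in applying the later mean from time zero.

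**Conclusion.** The point holds as a conditional one. The exposure rule and the start of follow-up are incompatible as written.

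- **By range:** with no true effect, a false excess at both low and high phosphate, HR about 1.1 to 1.3 in the extreme 5% in most settings tried, smaller with wider categories or many single-value patients.
- **Linear, no drift:** essentially unbiased under the null.
- **Linear, with drift:** biased in the direction opposite to the drift, about 0.96 per 0.15 mmol/L at an assumed +0.01 mmol/L per year.

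The mechanism follows from the protocol text alone; the sizes rest on the assumptions listed. The rule should be changed before analysis, because the planned analysis by range is affected even without drift and more data will not remove the bias.

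**What to change.** Delete the rule that assigns the later mean from time zero, and choose one of two main definitions in advance:

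1. **Landmark.** Average the values within a fixed window, for example the first 12 months, and start follow-up at the end of that window in patients still event-free and under observation.
2. **First value.** Use the time-zero value alone, with follow-up from time zero.

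A start-stop Cox model using the cumulative mean of the values recorded so far (up to five) can be added as an alternative. The protocol should then say that it addresses updated rather than baseline phosphate. If eGFR stays fixed at baseline, changing renal function may confound that analysis.

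Apply the same timing rule to all covariates, including the two-value eGFR and albumin:creatinine means: values at or before the start of follow-up only.

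**Cost.** Wording and data restructuring; the dated values are already needed for the planned mean. A 12-month landmark loses the first-year events, about 19% in simulation A (person-time 0.95 of 5 years per patient with uniform follow-up over 0 to 10 years). The first value loses none but is noisier: in simulation B, a true HR of 1.20 per 0.13 mmol/L of underlying phosphate was estimated at 1.09 to 1.10, against 1.12 to 1.14 with a 2-year landmark mean.
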